## Abstract

**Background:**

Infertility—the inability to achieve pregnancy despite ≥12 months of focused attempts to conceive—is experienced by 1 in 6 couples. Women typically carry a disproportionate share of the psychological burden associated with infertility, experiencing poor quality of life, and 30%-40% experiencing depressive mood or anxiety. Unfortunately, currently available psychological interventions targeting infertility-related distress are associated with modest effects.

**Objective:**

Our team, in collaboration with patient advisors, has designed a self-help intervention for infertility-related distress involving 7 weekly 10-minute videos addressing the cognitive, behavioral, and interpersonal challenges associated with infertility, delivered through a mobile app. A feasibility study suggests that it is well accepted and highly effective in reducing symptoms of anxiety and depressed mood among distressed individuals dealing with infertility. This study represents the next step in this line of research: a fully powered randomized controlled trial comparing the intervention to a waitlist control group.

**Methods:**

We will recruit 170 individuals struggling to become pregnant in Canada or the United States to be randomized to our 7-week self-help program or a treatment-as-usual condition. The primary outcome will be fertility quality of life, while secondary outcomes will include depressive symptoms, anxious symptoms, and relationship quality, assessed before and after the program as well as biweekly for 16 weeks following completion of the program. Self-reported health care use and the presence of diagnosed mood and anxiety disorders, assessed through a structured psychiatric interview, will also be assessed immediately following the intervention and at the 16-week follow-up assessment. Treatment adherence and retention will also be recorded throughout the intervention. Multilevel modeling will compare the intervention arm to the treatment-as-usual condition in terms of all continuous outcomes across the 9 measurement points. Logistic regression will be used to assess the occurrence of mood and anxiety disorders in the 2 treatment arms at the posttreatment assessment as well as at the 16-week follow-up. Sensitivity analyses will examine potential treatment moderators: membership in the LGBTQIA+ (lesbian, gay, bisexual, transgender, queer, intersex, and asexual) communities, baseline fertility quality of life, cultural background, disability status, and pursuit of conception through medical intervention.

**Results:**

We expect our intervention to be more effective than treatment-as-usual in improving all mental health parameters assessed and decreasing health care use related to both mental and reproductive health. Effects are expected to be larger with decreasing baseline quality of life and equally effective regardless of membership in the LGBTQIA+ communities, cultural background, or disability status.

**Conclusions:**

If our intervention is successful, this would suggest that it should be scaled up and made publicly available. The availability of this program would fill an important gap in light of the high rates of psychopathology among those experiencing infertility and considering the current lack of effective psychotherapy approaches for infertility.

**Trial Registration:**

Clinicaltrials.gov NCT06006936; https://classic.clinicaltrials.gov/ct2/show/NCT06006936

**International Registered Report Identifier (IRRID):**

PRR1-10.2196/52662

## Introduction

### Overview

The Canadian Community Health Survey reveals that 16% of Canadian reproductive-aged couples are currently infertile [1], defined as being unable to achieve pregnancy despite ≥12 months of focused attempts to conceive. Although male- and female-factor infertility are equally prevalent, women bear the brunt of the infertility-related burden as treatments require that women monitor their menstrual cycles, attend near-daily ultrasounds, self-inject gonadotropins, and undergo invasive and painful procedures. Women who travel for fertility treatments face additional psychosocial burdens, including schedule disruptions, time off work, and coordination of care among multiple health care providers. It is therefore not surprising that women carry a disproportionate share of the psychological burden associated with infertility, with infertile women consistently reporting lower self-esteem, more instances of depressed mood and anxiety, and lower life satisfaction than their male partners [2]. Lesbian couples pursuing sperm donation experience similar distress, with the intended pregnant individual being at higher risk for depression and anxiety relative to their partner [3].

Around 30%-40% of women presenting for the evaluation of infertility report clinical symptoms of depressed mood and/or anxiety [4-7]. In addition, research from our team [8] suggests that the COVID-19 pandemic has exacerbated distress amid fertility treatment suspensions and delays. Untreated symptoms of depressed mood and anxiety among women with infertility may, in turn, reduce the likelihood of achieving pregnancy, given that psychological burden is the most commonly cited reason for prematurely discontinuing fertility treatments [9]. In a study of 450 couples who were offered 3 government-funded in vitro fertilization (IVF) cycles, 54% did not complete all 3 cycles despite not achieving pregnancy, with “psychological burden” being the primary reason for discontinuing IVF [10]. It is critical that women with infertility who are distressed receive effective mental health treatment to reduce distress and improve conception rates.

Despite high rates of distress among women with infertility, currently available psychological interventions are often ineffective or associated with relatively small benefits. In our recent systematic review of psychological interventions for infertility-related distress [11], we observed that typical interventions are associated with a small beneficial effect on anxiety but a nonsignificant effect on depressive mood, marital quality, or quality of life. Our conclusions confirm findings from a previous meta-analysis [12] and those of a recent review [13] concluding that “a new intervention (targeting infertility-related distress) should be developed.”

### Intervention Development

This trial seeks to test the efficacy of a novel infertility-specific intervention. In developing a treatment that is designed to improve upon the limitations of current approaches, we have used a methodical and evidence-based framework in designing and refining our intervention, using the Medical Research Council [14] and National Institute of Health’s ORBIT Model [15] for trial design interventions as guides. Specifically, we have completed the following milestones to date: (1) completed a systematic review of available interventions, (2) conducted a needs-based assessment using qualitative research methods, (3) carried out an evaluation of potential intervention components, and (4) performed a preliminary test of the acceptability and effect of our newly developed intervention. These steps are described in greater detail below.

#### Systematic Review and Meta-Analysis

As a starting point, we conducted a systematic review and meta-analysis of psychological interventions for infertility [11,16], which included an examination of treatment moderators such as psychotherapeutic approach (eg, mindfulness-based approaches vs cognitive behavioral therapy) and therapy format (eg, self-administered vs group). This process not only confirmed that currently available interventions were largely ineffective but also revealed that neither therapeutic approach nor format significantly impact treatment benefits.

#### Qualitative Needs Assessment

Our team then used semistructured interviews with women with infertility and mental health professionals specializing in infertility to identify the unique aspects of infertility-related distress [17]. Table 1 depicts the themes and subthemes identified. Unique features include the avoidance of infertility reminders (eg, pregnant women and children), excessive cognitive and behavioral focus on one’s infertility to the exclusion of previously enjoyed activities, and negative interactions with loved ones perceived as insensitive.

**Table 1 table1:** Themes and subthemes of infertility-related distress identified through a qualitative research project by our team [17].

Theme 1: anxiety	Theme 2: mood disturbance	Theme 3: threat to self	Theme 4: threat to couple	Theme 5: weakened social support
Anxious rumination	Emotional lability	Unmet expectations for self and one’s future	Differences in coping	Strained romantic relationship
Avoidance of infertility reminders	Helplessness	Shame	Sexual dysfunction	Social stigma
Narrowed focus on infertility-related activities	Emotional exhaustion	Self-blame	Financial stress	Social isolation
Excessive information seeking	N/A^a^	N/A	Disagreement on next steps	Dismissal by health care providers

^a^N/A: not applicable.

In addition to identifying clear psychological targets for our intervention, this study also aimed to clarify which interventions were currently being used by practicing clinicians. Our findings indicated a near-universal use of an eclectic and unstructured approach associated with the widely held opinion that no existing therapeutic approach sufficiently addresses all of the biopsychosocial factors contributing to infertility-related distress.

#### Evaluation of Potential Intervention Components

The next step in our intervention development was to identify and consider all candidate techniques that might effectively target the psychological challenges identified as being common in infertility. To do so, we identified all of the psychotherapeutic approaches endorsed by the American Psychological Association’s Clinical Section as being evidence-based for the treatment of anxiety, mood disorders, relationship difficulties, and chronic illness. The 5 identified approaches were then further broken down into their component procedures, resulting in a total of 14 different psychological techniques. In collaboration with a panel of patient advisors and using lay language, we described how each of these techniques would look when applied to infertility-related distress and what their purpose would be. We then surveyed a total of 644 women from online infertility-specific support groups [18], asking them to rate the perceived usefulness of each of the 14 techniques while asking them to identify up to 5 that were “most liked” and “most hated.” Participants were also given the opportunity to provide written feedback on each of the techniques, such as how they might be better tailored to infertility. We then presented the results of this survey to our panel of patient advisors and collaboratively decided on the content of our intervention. We decided on 6 core modules plus a bonus module, the content of which is described in Textbox 1 [18].

Chosen modules based on a survey of 644 women with infertility [18] and collaboration with patient advisors. Mean helpfulness ratings for each module, as assessed in a feasibility study of 21 women, are shown.
**Modules and focus**
Cognitive restructuring: identifying and challenging the extreme negative thoughts that contribute to a depressive and anxious mood (eg, “In vitro fertilisation will never work”).Challenging core beliefs: identifying and challenging unhelpful deep-seated beliefs about themselves, other people, and the world that are perhaps not based on reality (eg, “nothing ever works out for me”). It involves looking for patterns in one’s thinking from the first module.Behavioral activation: identifying activities that have been dropped or engaged in less because of an increased focus on infertility. Aim to reintegrate these previously enjoyed activities into their day-to-day lives.Sharing your grief: learning about different styles of coping and how clashes in coping styles can lead to conflict within a couple. The individual is instructed on how to engage their partner in a structured conversation about how each can help the other in times of grief, such as following a negative pregnancy test.Strengthening your relationship (bonus module): provides evidence-based information about how to better connect with one’s partner in general. Was offered along with Module 4 for those experiencing relationship distress.Living your values (ie, stopping avoidance): reflecting on one’s overarching life values and considering how one’s daily actions align with those values. Indirectly addresses avoidance that is common among individuals with infertility (eg, withdrawing from friends and family and avoiding children and pregnant women). Encourages the individual to consider ways in which they can reduce avoidance without worsening their distress.Summary or wrap up: providing an overview of the program’s content and encouraging the individual to reflect on what’s been accomplished as well as areas for further development.

When it came time to decide on the format of our intervention, a self-help internet-delivered intervention was chosen for several reasons. First, the findings from our systematic review indicate that self-administered interventions are as effective in improving mental health as other, more costly formats. Second, when asked what format a new intervention should take, 71% (15/21) of women from our needs assessment qualitative study responded that it should be self-delivered through the internet. Third, we reasoned that this format could be most effectively scaled up and made accessible to diverse populations of women and in regions with limited access to psychological services. Thus, in close collaboration with our patient advisors, each module was translated into a 10-minute PowerPoint (Microsoft Corp) slideshow with professional voiceover. A mobile app was then developed to increase accessibility to the modules.

#### Preliminary Testing of Our New Infertility-Specific Intervention

With a new program developed and fully vetted in consultation with our patient advisory panel, we conducted a pilot study of 21 women recruited through local support groups, assessing intervention acceptability [19]. All participants exhibited clinically significant levels of infertility-related distress, as indicated by a Fertility Quality of Life Scale (FertiQoL) score ≤52 [20]. Enrolled through a Zoom (Zoom Video Communications)-administered enrollment session, participants received 1 module per week through email and were asked to view the 10-minute slideshow within 24 hours of receipt. Midweek, they received an email reminder of the homework assignment, encouraging them to apply their homework assignment throughout the week. At the end of each week, participants were asked to rate the extent to which the module and homework were perceived as helpful in lowering their distress (0-10). At baseline and each week, participants completed the Generalized Anxiety Disorder-7 (GAD-7) and 9-item Patient Health Questionnaire (PHQ-9); the FertiQoL was completed at baseline and after the intervention. Each week and in an interview at the end of the study, participants provided written and verbal feedback, respectively, on the intervention.

Of the 21 women enrolled in the study, 2 became pregnant and were removed from the program prematurely (all outcomes assessed until the point of pregnancy were analyzed). Of the remaining 19 women, 15 completed all 6 modules, and 4 completed a portion of the program. Data from all 19 women were included in the analysis. The average helpfulness rating of each module was found to be 7.4 or above out of 10. Fertility quality of life increased by an average of 12 points out of 100, translating to a Cohen *d*=0.9. Large reductions in both mean symptoms of anxiety and depressed mood were observed (pre-to-post Cohen *d*=–1.2 and –1.3, respectively, where effects above 0.8 are considered large), corresponding with clinically meaningful improvements. In addition, 85% of participants experienced a clinically significant decline in either anxious or depressive symptoms (defined as a change of 4 points on the GAD-7 [21] and 5 points on the PHQ-9 [22]).

While the intervention was successful, areas for improvement were identified. For example, homework assignments were modified to include examples of completed homework. Participants reported that our “bonus” relationship module deserved to be a core part of the program, extending it to a total of 7 weeks.

### The Current Trial

Over the last 3 years, our team has carefully designed a self-help intervention for infertility-related distress that is patient-informed and developed using best practices in intervention design. Results from this feasibility study suggest that it is well accepted and effective in increasing quality of life and reducing symptoms of depressed mood and anxiety among women with infertility-related distress. The proposed project, a sufficiently powered randomized controlled trial comparing the intervention to a treatment-as-usual control group, is the next step in this line of inquiry. It is hypothesized that the intervention will result in greater increases in fertility quality of life and relationship quality as well as decreases in symptoms of depressed mood and anxiety relative to a treatment-as-usual condition, and that these improvements will be maintained over a 16-week follow-up assessment period.

If the proposed trial confirms that the intervention is effective in improving quality of life and mental health symptoms among those with infertility, our next step will be to make this program widely available to women, including making the intervention available through YouTube and engaging our collaborating knowledge users and partner organizations to promote it widely. We will also aim to tailor the program for diverse and marginalized underserved groups.

## Methods

### Trial Design

The proposed research is a single-blind randomized controlled trial comparing the above-described self-help program to a waitlist control condition. As the project requires no in-person contact, we will recruit women living throughout Canada and the United States. Fertility quality of life, infertility-related distress, symptoms of depressed mood and anxiety, and relationship quality will be assessed before and after the program, as well as every other week for 16 weeks.

### Treatment Conditions

#### Intervention Condition

Participants will be given access to a 10-minute module video per week through a mobile app created for this trial. Midweek, participants will receive an automated email reminder of the homework assignment for that week, encouraging them to incorporate the homework into their daily lives. Participants will be permitted to engage in any other psychological interventions they wish but will be asked to report other psychological interventions accessed at the end of their participation.

#### Treatment-As-Usual Control Condition

Participants assigned to the control condition will be instructed to continue their pursuits to conceive without accessing the self-help program. They will be permitted to access other psychological resources that are available to them, though, like the intervention condition, they will be asked to report any treatments accessed in the postintervention survey. They will complete the outcome measures at the same time as participants in the treatment condition. Following completion of the study, the control group will be offered the program in the same manner as the treatment group.

In the original funded grant protocol, we had proposed a waitlist control condition in which participants were not permitted to access other mental health services; however, we have since changed the control condition to treatment-as-usual in order to more accurately estimate the real-world effectiveness of the treatment. This change also allows us to open the trial to individuals reporting suicidal ideation because these participants will likely require additional mental health services while participating in the current trial.

### Randomization Scheme

The Clinical Research Support Unit at the University of Saskatchewan will create the randomization scheme and provide the principal investigator with opaque envelopes containing treatment assignments, ensuring that the research team has no control over the assignments. Randomization will take place at the end of each enrollment session, after the baseline surveys have been completed, and will be stratified based on whether a woman is undergoing fertility treatments or attempting to conceive without medical intervention, as this will be a potential moderating variable.

### Protecting Against Sources of Bias

A number of strategies will be used to protect against bias. First, the trial will be registered with clinicaltrials.org before any data collection commences. Second, as described above, the randomization scheme will be created by a third party, and the study research assistants will be instructed to strictly adhere to the randomization protocol without exception. Third, though it is not possible to maintain full blinding of either the participant or research team given the nature of the intervention, all outcomes will be collected by a research assistant who is blind to the participant’s treatment allocation. Fourth, an intent-to-treat approach will be taken in analyzing the results—every effort will be made to continue to collect outcome data on all participants, regardless of whether participants dropped out of the intervention early or not. Final, we will follow the CONSORT-SPI (Consolidated Standards of Reporting Trials for Social and Psychological Intervention Trials) reporting guidelines [23] in reporting the results of the trial, strictly adhering to the original trial protocol. Any deviations will be clearly described and justified.

### Participants

#### Inclusion and Exclusion Criteria

Based on our sample size calculations, we will recruit 170 women, recruited through the web. The inclusion criteria will include the following: is infertile as defined as either actively attempting to conceive for ≥12 months without success or is currently undergoing fertility treatments (eg, ovulation induction medication, IVF, and intrauterine insemination). This definition ensures that this study is inclusive of both individuals who cannot afford fertility treatments and women who are in same-sex couples and cannot conceive naturally. Though the original funded protocol excluded individuals reporting active suicidal ideation, those already receiving psychotherapy, and those with high levels of fertility-related quality of life (FertiQoL above 70), we have since decided to remove these exclusion criteria in order to closely estimate the program’s anticipated real-world effectiveness. Rather than exclude individuals based on baseline quality of life, we will perform secondary analyses, considering baseline quality of life as a treatment moderator.

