#### Participant Screening and Enrollment

Prospective participants will be emailed the link to a web-based eligibility survey. If found to be eligible, they will be asked to provide their contact information, and a research assistant will contact them to schedule an enrollment session through videoconference.

During the Zoom-facilitated remote enrollment session, eligibility will be confirmed, a brief introductory video explaining the study and intervention will be presented, and consent will be obtained. An enrollment session in which visual contact is made will ensure that our recruited participants are not simply “bots” posing as eligible participants. During the session, participants will complete the baseline questionnaires through a link emailed to them by the research assistant. Upon completion of the questionnaires, the research assistant will open an opaque envelope, revealing the participant’s random assignment to either the treatment or control condition. The research assistant will then ask the participant which day of the week they would like to receive their weekly module video (if assigned to the treatment condition) or weekly outcomes survey (if assigned to the control condition).

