#### Participant Safety

Participants endorsing suicidal ideation on question 9 of the PHQ-9 at baseline will be permitted to participate in the study but will be informed that their level of risk will be reassessed weekly. Specifically, each week, they will receive a survey question, “Please pick out the one statement that best described how you have been feeling during the past week, including today: (A) I don’t have any thoughts of killing myself. (B) I have thoughts of killing myself, but I would not carry them out. (C) I would like to kill myself, or (D) I would kill myself if I had the chance.” If participants choose either C or D, a message including contact information for 2 suicide hotlines will appear. As well, an automatic notification will be sent to the study therapist, flagging the response. They will then follow up with the participant immediately by phone, at most within 24 hours. If participants endorse A or B, they will simply be allowed to continue with the program.

In addition, the presence of active suicidal ideation (presence of a plan or intent) will be assessed by the researcher during the Zoom-facilitated enrollment session. Those endorsing active suicidal ideation will be referred to additional in-person mental health resources available in their geographic area. They will be given access to the program for their own benefit but will not be enrolled in the study.

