#### Depressive Symptoms

Self-reported symptoms will be assessed using the PHQ-9 [26], a 9-item measure assessing symptoms in the last 2 weeks that closely parallels the criteria for major depressive disorder as defined by the *Diagnostic and Statistical Manual of Mental Disorders, Fifth Edition* (DSM-5) [27]. Internal consistency coefficient (ICC) has been estimated at α=.89 and test-retest reliability at r=0.84. The PHQ-9 has been shown to be superior to other questionnaires in detecting changes in depressive mood following treatment [28]. Participants endorsing suicidal ideation on item 9 of the PHQ-9 will be required to answer a weekly question.

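### The eligibility section says the exclusion for active suicidal ideation was dropped, but the safety section still applies it and ties the weekly risk question to ideation endorsed at baseline

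*Protocol article*

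**What the plan says.** **Eligibility.** The Inclusion and Exclusion Criteria section reports three exclusions in the funded protocol. The sentence begins "Though the original funded protocol excluded individuals reporting active suicidal ideation, those already receiving psychotherapy" and adds a high FertiQoL score (above 70). It then says of the three: "we have since decided to remove these exclusion criteria". The reason given is to come closer to real-world effectiveness. The Treatment-As-Usual Control Condition section likewise says the change of control condition opens the trial to people who report suicidal ideation, without separating ideation with a plan from ideation without one.

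**Safety.** Under Participant Safety, "the presence of active suicidal ideation (presence of a plan or intent) will be assessed by the researcher during the Zoom-facilitated enrollment session". Those who endorse it are referred to in-person care, and "They will be given access to the program for their own benefit but will not be enrolled in the study".

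**Monitoring.** The same section says "Participants endorsing suicidal ideation on question 9 of the PHQ-9 at baseline will be permitted to participate", on the footing that their risk is reassessed weekly by a four-option question. If either of the two most severe options is chosen, hotline contacts are displayed and "an automatic notification will be sent to the study therapist, flagging the response", with a call within 24 hours. The Depressive Symptoms section gives the trigger with no time point: "Participants endorsing suicidal ideation on item 9 of the PHQ-9 will be required to answer a weekly question".

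**Order of enrollment.** Participant Screening and Enrollment says "Upon completion of the questionnaires, the research assistant will open an opaque envelope", which reveals the allocation.

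**The concern.** There are two separate problems.

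First, the eligibility section names active suicidal ideation as an exclusion that no longer applies, and the safety section applies it. A reader who relies on the eligibility section would believe that the results cover people with active ideation, when those people are turned away. The real-world rationale offered for dropping the exclusion is overstated to that extent. Staff following one section would enroll people whom the other section refuses.

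Second, the trigger for weekly risk monitoring is worded in two ways. The hotline message and the therapist alert depend on the answer to the weekly question; neither is attached to PHQ-9 item 9 itself. If only a baseline endorsement starts the weekly question, a participant who first endorses item 9 later sets off none of these responses. The trial is run remotely, its follow-up questionnaires are emailed web surveys, and it deliberately admits people with suicidal ideation, so the text should leave no doubt about what happens.

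**Working it through.** **1. Eligibility, section against section**

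| Section | Status of active suicidal ideation |
|---|---|
| Inclusion and Exclusion Criteria | Formerly an exclusion; now removed |
| Treatment-As-Usual Control Condition | Trial opened to suicidal ideation, with no qualifier |
| Participant Safety | Defined as plan or intent; assessed at enrollment; not enrolled |

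The removal sentence in the first row describes the present criteria, so this is not merely a difference from superseded text. The third row uses the same term, defines it, and gives the opposite consequence. Because it is the only one of the three that sets out a procedure, it is the one staff would follow, and the first row is the one in error.

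**2. Order relative to randomisation**

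The Randomization Scheme section places randomisation at the end of the enrollment session, after the baseline surveys. Participant Safety says only that plan or intent is assessed during that session. The intended order can be inferred but is not written down. If the assessment came after the envelope was opened, a refusal would be a post-randomisation removal, which would conflict with the intent-to-treat commitment under Protecting Against Sources of Bias.

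**3. Number of later PHQ-9 administrations**

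Inputs: the Overview under Primary and Secondary Outcomes schedules self-reported outcomes at the end of week 7 and then every 2 weeks for 16 weeks. Statistical Analyses gives 9 outcome measurement points.

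- Biweekly follow-ups: 16 / 2 = 8
- Post-baseline administrations: 1 + 8 = 9, which agrees with the stated 9
- Weeks: 7, 9, 11, 13, 15, 17, 19, 21 and 23 (7 + 16 = 23)

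**4. What item 9 triggers at each time**

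| Item 9 first endorsed | Participant Safety, read literally | Depressive Symptoms wording |
|---|---|---|
| At baseline | Weekly question, with hotline message and alert for the two most severe answers | Same |
| At any of the 9 later surveys | No response stated | Weekly question starts |

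The number of surveys without a stated response is therefore 9 on the literal safety wording and 0 on the other.

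**5. Illustrative number of participants**

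The article gives no rate of new ideation after baseline. Assuming a share p of the 170 recruited:

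- p = 1%: 170 × 0.01 = 1.7
- p = 5%: 170 × 0.05 = 8.5
- p = 10%: 170 × 0.10 = 17

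The 170 includes people who endorse item 9 at baseline and people who later drop out. With the 128 participants whom the power calculation expects to remain, the same range is 128 × 0.01 = 1.28 to 128 × 0.10 = 12.8. These figures show scale only; the conclusion does not depend on them.

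**6. Sample size**

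Cohen f = 0.25 with two groups is d = 0.5. At two-sided α = .05 and 80% power this needs 63.77, so 64, per arm, or 128 in total. Allowing for dropout, 128 / (1 − 42/170) = 170. The plan's figures reproduce, and nothing in this point alters them.

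**The case against.** The conflict of wording on eligibility has to be conceded, but it can be argued that little follows from it. Participant Safety is clear and operative, the control-condition section describes the change without the word active, and the likely error is that one word in the eligibility section. What the funded protocol meant by the term cannot be checked, because that protocol is not shown. Randomisation already comes at the end of the session in which eligibility is confirmed. The other two dropped exclusions are not contradicted anywhere.

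On monitoring, Participant Safety never says that only baseline endorsement counts. Its sentence can be read as a condition of entry, compatible with the open-ended rule under Depressive Symptoms. Detail on later-emerging ideation might sit in the full protocol. Two post-intervention diagnostic interviews give further contact with participants, and that surveys are completed alone is an inference. The content of the weekly survey for controls is not stated, so the count of PHQ-9 administrations in that arm is not beyond doubt. The participant range rests on an assumed rate and a denominator that is too large.

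Much of this stands as qualification. The one-word explanation is plausible, and the fix would write it down. The monitoring gap exists on one reading only, and the counts are illustrations. Two things do not stand. The eligibility section as written is wrong about who is enrolled. And the article does not leave the safety procedure to another document: it gives the question, the response options and the 24-hour limit, then states the trigger in two ways. The interviews cover two of the nine later time points, and the article assigns them no suicide-risk response.

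**Conclusion.** The concern holds on both points and should be fixed.

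The eligibility contradiction is certain from the text and concerns every applicant with a plan or intent; the article does not give their share. It affects the description of the trial population and the claim to real-world coverage.

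The monitoring point is an inconsistently stated trigger. Its size depends on which section governs: nine later surveys with no stated response under the literal Participant Safety wording, none under the Depressive Symptoms wording. About 2 to 17 participants would be concerned if 1% to 10% of 170 first endorsed item 9 after baseline, which is an assumption.

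Sample size and the primary analysis are unaffected.

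**What to change.** 1. **Inclusion and Exclusion Criteria.** State that suicidal ideation without plan or intent is now admitted, and that ideation with plan or intent remains an exclusion. State that this is assessed at the enrollment session before the allocation envelope is opened, and that those turned away are counted as pre-randomisation exclusions.
2. **Participant Safety and Depressive Symptoms.** Use one rule in both: endorsing item 9 at any PHQ-9 administration, baseline or later, in either arm, starts the weekly risk question with its existing hotline message and therapist alert.

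The cost is a protocol clarification, an ethics notification, one change to the survey logic, and some additional follow-up calls by the existing study therapist. Neither the number recruited nor the primary analysis changes.
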